### Secondary outcomes

The differences on the MBI, SF-36, and the results of BOLD-*f*MRI examination after intervention are considered as the secondary outcome measures.

The MBI
[32] is a widely used tool, measuring the extent to which somebody can function independently and have mobility in their activities of daily living (ADL), and also indicating the need for assistance in care. It contains 10 items and is scored on a scale from 0 to 100 with a higher score indicating more independence
[33].

The SF-36
[34] is a short-form health survey with 36 questions. It yields an 8-scale profile of functional health and wellbeing scores, as well as psychometrically-based physical and mental health summary measures and a preference-based health utility index. It is a generic measure, regardless of age, disease, or treatment group. The SF-36 has proven useful in differentiating the health benefits produced by a wide range of different treatments.

The BOLD-*f*MRI is the primary form of functional magnetic resonance imaging, and it is a type of specialized brain scan used to map neural activity in the brain of humans or other animals by imaging the change in blood flow (hemodynamic response) related to energy use by brain cells
[35]. The procedure is similar to MRI but uses the change in magnetization between oxygen-rich and oxygen-poor blood as its basic measure. The resulting brain activation can be presented graphically by color-coding the strength of activation across the brain or the specific region studied. The technique can also localize activity to within millimeters.

### Safety assessments

All of the adverse events (AEs) that happen during the treatment and follow-up period will be recorded in detail by researchers and therapists at each CHC. Serious adverse events will be reported to the Human Research Ethics Committee (HREC) of FJTCM immediately, who will make a judgment on whether the participant can continue in the trial depending on the patient’s condition. Any adverse event will be analyzed regardless of the causality related to intervention and will receive corresponding treatment measures.

### Economic evaluation

The indicator of economic evaluation will employ a cost-effectiveness ratio, meaning the required cost of every point increased on the CRRCAE. The cost of interventions consists of direct costs and indirect costs. Direct costs will include any expense involving treatments throughout the rehabilitation period. The number of workdays lost by participants and care-givers owing to illness will be counted in indirect costs. Finally, there will be a comparison on the differences of cost-effectiveness ratio between CHCs and high-grade hospitals.

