### Participants and recruitment

The protocol will be carried out at community health centers (CHCs) run by three sub-centers, including the Affiliated Rehabilitation Hospital of Fujian University of Traditional Chinese Medicine (Fujian province, China), the Second Affiliated Hospital of Shandong University of Traditional Chinese Medicine (Shandong province, China), and the First Affiliated Hospital of Henan College of Traditional Chinese Medicine (Henan province, China). Many CHCs in different areas of the three provinces will be included in this protocol, providing a large number of patients.

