### Randomization and blinding

Each participating CHC will be assigned to either experimental group or control group by restricted randomization generated by an independent statistician, who works in the evidence-based center of FJTCM, via SAS software (Version 8.2, SAS Institute, Cary, North Carolina, United States). The random allocation sequence is blinded to the screeners who make the baseline test for the patients, and protected by a specified project manager who is not involved in the recruitment program of this study. Both allocation and baseline measurements will be concealed to outcome assessors.

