### Intervention

Participants in the experimental group will receive integrated acupuncture therapy with SLT and initial therapies, meanwhile the control group will only receive SLT and initial therapy. The initial therapy consists of health education and conventional medical therapy. The treatments will take place five times per week for 4 weeks in total. All of the employees participated in this trial will be standardized in their training, including in the study protocol, methods of treatments, and assessments.

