### Outcome measures

Except for baseline (-2 to -1 weeks), all of the primary and secondary outcomes assessment will be also conducted at end of 2-week treatment (3 weeks), end of 4-week treatment (5 weeks), end of 6-week follow-up (11 weeks), and end of follow-up period (17 weeks) with a BOLD-*f*MRI examination only at end of the 4-week treatment (5 weeks). A summary of all the measures in the trial is shown in Table 
1.

**Table 1 T1:** Trial processes chart

**Items**		**Before enrolment (weeks) -2 to (-1)**	**Intervention period (weeks) 1 to 2**	**End of 2-week treatment (weeks) 3**	**Intervention period (weeks) 3 to 4**	**End of 4-week treatment (weeks) 5**	**Follow-up (weeks) 5 to 10**	**End of 6-week follow-up (weeks) 11**	**Follow-up (weeks) 11 to16**	**End of 12-week follow-up (weeks) 17**
Recruitment		**×**								
Enrolment		**×**								
Inclusion criteria		**×**								
Exclusion criteria		**×**								
Informed consent		**×**								
Basic characteristic variables		**×**								
Randomization and allocation concealment		**×**								
Primary outcomes	Speech function	**×**		**×**		**×**		**×**		**×**
	Severity of aphasia	**×**		**×**		**×**		**×**		**×**
Secondary outcomes	Activities of daily life	**×**		**×**		**×**		**×**		**×**
	Quality of life	**×**		**×**		**×**		**×**		**×**
	Functional condition of the brain	**×**				**×**				
Adverse events recorded			**×**		**×**		**×**		**×**	
Self-reported drug therapy			**×**		**×**		**×**		**×**	
Cost sheet of rehabilitation therapy			**×**		**×**		**×**		**×**	

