## Discussion

Nearly 20 to 25% of all stroke patients suffer from aphasia
[36], and approximately half of the initially affected patients still suffer from aphasia one year after stroke
[10,12]. Acupuncture, which proved to have a positive therapeutic effect on aphasia in acute stage stroke patients
[37], is considered as a good choice for chronic stroke patients with aphasia searching for complementary and alternative medicine as longterm treatment at a low cost.

We adopt a randomized, parallel-controlled, single-blind design in this trial to guarantee the quality level of the study. In consideration of the characteristics of stroke-induced aphasia, we will investigate the value-in-apply of combined SLT to scalp acupuncture treatment from the view of safety and efficacy, by the way of comparing the cost-effectiveness ratio of aphasia rehabilitation between CHCs and high-grade hospitals. We will also judge the longterm stability of improvements by a 12-week follow-up after intervention and dynamically observe the changes of curative effects by setting five assessment points (baseline, 2 and 4 weeks after intervention,6 and 12 weeks after follow-up).

A number of studies have come to an agreement that aphasia treatment is effective in enhancing recovery
[38-41]. However, there is a controversy about the role of the course of disease on outcomes. Some trials hold the view that further improvement of language abilities is very limited beyond 6 months after the onset of stroke
[42] and therapy provided immediately after stroke results in more beneficial effects than deferred treatment
[43].Others think that language abilities can be significantly improved in the chronic stage after a stroke when training is sufficiently intensive
[44-47]. In the present trial, if possible, we intend to make a stratified analysis according to the course of the disease to discover the best time to start treatment. In addition, cortical plasticity is recognized as the main mechanism of functional recovery basing on neuroimaging findings
[48-50]. In this study, we will use *f*MRI to observe the changes of activation of brain hemisphere structures attributed to the treatment.

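### The economic evaluation states only a CHC-versus-hospital contrast, which the randomised design does not provide, and uses a cost-per-point ratio that does not show what adding acupuncture buys

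*Protocol article*

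**What the plan says.** The Economic evaluation section of the protocol article defines its indicator as "a cost-effectiveness ratio, meaning the required cost of every point increased on the CRRCAE". It counts direct treatment costs and workdays lost, and closes with the one comparison it names: "there will be a comparison on the differences of cost-effectiveness ratio between CHCs and high-grade hospitals". The Discussion says the value of combining SLT with scalp acupuncture will be investigated "by the way of comparing the cost-effectiveness ratio of aphasia rehabilitation between CHCs and high-grade hospitals".

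The design sections describe something else:

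- Setting (Participants and recruitment): "The protocol will be carried out at community health centers (CHCs) run by three sub-centers". The three sub-centers are hospitals, but they appear as the bodies that run the CHCs.
- Unit of allocation (Randomization and blinding): "Each participating CHC will be assigned to either experimental group or control group by restricted randomization".
- Treatment contrast (Intervention section): both arms get SLT and the same initial care, and only the experimental arm gets acupuncture as well.
- Cost data (Table 1, under Outcome measures): a line headed "Cost sheet of rehabilitation therapy", marked for both treatment periods and both follow-up periods.

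No section states a cost or cost-effectiveness comparison between the two randomised arms.

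**The concern.** The Background gives the goal as a programme that is both effective and economical, and the Abstract lists economic effects among the other outcomes. The economic question that randomisation can answer is what acupuncture adds to cost and to language gain when given on top of SLT. The stated comparison instead sets one care setting against another. Patients treated in high-grade hospitals may differ from CHC patients in severity, time since stroke and treatments received, and allocation does nothing to balance these differences.

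The ratio has a separate weakness. Dividing cost by points gained credits every point to the spending. The article itself says that recovery tends to plateau only by one year after onset, admits patients up to two years after stroke, and concedes in its Discussion that early spontaneous recovery cannot be eliminated as a confounder. Part of each arm's gain would have come without the added treatment.

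If the plan is followed as written, the economic half of the goal rests on an unrandomised contrast and on a ratio that answers a different question.

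**Working it through.** **1. Where the planned patients are.** The Economic evaluation section gives no figure to reproduce. The Sample size section does, and it shows how the patients are allotted. Inputs: π1 = 0.6471, π2 = 0.85, m = 16, ρ = 0.030, two-sided α = 0.05, power 90%.

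- Design effect: 1 + (16 − 1) × 0.030 = 1.45.
- n = (1.960 + 1.282)² × [0.6471 × 0.3529 + 0.85 × 0.15] × 1.45 / 0.2029² = 131.7, so 132 per group, as stated.
- Total with 10% added: 2 × 132 × 1.10 = 290.4, which matches the stated 290.

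The two CHC-randomised arms therefore use up the whole planned sample. No patients are allotted to a hospital group.

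**2. Planned comparison against available comparison.**

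| | Stated economic contrast | Randomised contrast |
|---|---|---|
| Groups | CHCs v high-grade hospitals | SLT + acupuncture v SLT, all at CHCs |
| Allocation | none described | CHCs, restricted randomisation |
| Costs scheduled | CHC side only, in the described design | both arms (Table 1) |
| CRRCAE change scheduled | CHC side only, in the described design | both arms (Table 1) |
| What a difference reflects | setting, case mix and treatment together | adding acupuncture |

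**3. What the ratio measures.** Let C0 and E0 be mean cost and mean CRRCAE gain in the SLT arm, and C1 and E1 those in the acupuncture arm. Write E0 = S + L (spontaneous recovery plus SLT effect) and E1 = S + L + A, where A is the effect of adding acupuncture.

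- Average ratio, acupuncture arm: C1 / E1 = C1 / (S + L + A).
- Incremental ratio: (C1 − C0) / (E1 − E0) = (C1 − C0) / A.

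S and L cancel, in expectation, only in the second. The two are linked by an identity:

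C1/E1 = (E0/E1) × (C0/E0) + (A/E1) × [(C1 − C0)/A].

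The acupuncture arm's average is thus a weighted mean of the SLT arm's average and the incremental ratio. The incremental ratio gets weight A/E1 only. When acupuncture adds little to a gain that would largely have occurred anyway, that weight is small, and the average stays close to the SLT arm's value whatever the added points cost. The incremental figure may lie above or below the averages, so the direction is not known in advance.

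**4. Number of clusters.** At 16 or more patients per CHC, 290 / 16 = 18.1, so at most about 18 CHCs, or about 9 per arm. If the planned ρ of 0.030 also held for costs or net benefit (an assumption, since it is given for the sample-size calculation), an interval that ignored clustering would use a standard error too small by a factor of √1.45 = 1.20.

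**The case against.** The article condenses a fuller protocol, and an external source of hospital costs could be named there. That is fair. A reader might infer that the investigators have no hospital data at all, but the article supports only the narrower statement that none appears in the described design. The mention of hospital admission under Health education concerns brochures and sets up no comparator. The core is unaffected: with a good hospital source, the contrast would still be unrandomised and could not isolate acupuncture, which is what the Discussion uses it for.

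The article never calls the ratio an average, and a between-arm calculation could sit in a separate economic plan. This also has force. But the wording divides cost by points gained with no difference between arms, and the section does choose a comparison, a different one. That makes this a stated choice and not only missing detail.

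Three stronger readings are not supported:

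- That lost workdays go unrecorded because Table 1 shows only a cost sheet. The contents of that sheet are not shown, and the Economic evaluation section includes workdays.
- That the ratio should be rejected because it is undefined at zero gain. An incremental ratio has the same problem when the arms do not differ.
- That the average misstates the incremental cost by some particular amount. With no costs or gains in the article, any such figure would be invented.

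Economic effects also rank below the primary and secondary outcomes, which limits the weight of the point.

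**Conclusion.** The point holds in this form. The only stated economic comparison is one the randomised design does not provide, and the stated indicator, as worded, does not measure the cost of what acupuncture adds. In the described design all 290 patients fall in the two CHC arms and none in a hospital comparator. No numerical bias can be given.

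The conclusion rests on two readings. One is that the article's account of arms and setting is complete as to the randomised design. The other is that cost per point gained means cost divided by gain, the natural sense of the words. The change should be made because it bears on a stated goal, but it does not touch the primary efficacy comparison. The Discussion's remark about relieving financial burden relative to high-grade hospitals is conditional on success. As the design is described, a randomised comparison would not support it.

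**What to change.** Restate the economic analysis as a comparison between the randomised arms. Report the difference in mean cost and the difference in mean CRRCAE change over the same period, each with an interval. Combine them as an incremental ratio or, preferably, as net benefit, λ × (E1 − E0) − (C1 − C0), where λ is the value placed on one CRRCAE point. The article gives no value for λ, so show results over a range. Net benefit stays defined when the arms differ little in effect.

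The interval must allow for clustering by CHC and for the small number of CHCs, for example by analysing CHC-level means with a t distribution on the number of CHCs minus 2 (at most about 16) degrees of freedom. A bootstrap that resamples about 9 CHCs per arm may give unreliable intervals and should not be relied on alone.

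Drop the hospital comparison, or name its source of costs and CRRCAE gains and label it descriptive and non-randomised. Bring the matching sentence in the Discussion into line.

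The cost is mainly wording and analysis. Table 1 already schedules the cost sheet and the CRRCAE, so the comparison needs no new patients or visits. What is given up is a trial-based claim about hospitals.

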### Statistical methods

Statistical analysis in this study will be performed by a statistician who is not involved in this trial and works in the Center of Evidence-based Medicine in FJTCM. Analysis of all data will be conducted with SAS software (version 8.2, SAS Institute, Cary, North Carolina, United States), and two-sided *P* < 0.05 was considered statistically significant.

Descriptive statistics will be expressed in different forms according to the types of the data in each group. That is to say, continuous variables will use mean and standard deviation for normal distribution, with median and interquartile range for non-normal distribution, and categorical variables will use proportions with their standard error. Comparison of baseline characteristics, the primary or secondary outcomes between groups will use the *t*-test or Mann-Whitney test for continuous variables and Pearson chi-squared or Fisher’s exact test for categorical variables. Changes in effect sizes of primary or secondary outcomes from baseline to each time point for two groups will be expressed using the paired *t*-test or Wilcoxon signed-rank test.

The primary outcomes will be analyzed using full analysis set (FAS) and per protocol set (PPS), with the secondary outcomes using FAS. Analysis of the primary and secondary outcomes should be on the basis of the intention-to-treat (ITT) population. The safety set (SS) will be used to assess adverse events.

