**Methods/Design:**

In a randomized controlled clinical trial with blinded assessment, 290 eligible patients with aphasia due to stroke will be randomly allocated into a control group or an experimental group. The course of this trial will comprise a 4-week intervention and a 12-week follow-up period. Five assessment points, including baseline, 2 and 4 weeks after treatment, 6 and 12 weeks after follow-up, are set to dynamically observe the changes of curative effects. Primary outcome measures are the differences in the score on both the China rehabilitation research center aphasia examination (CRRCAE) and Boston diagnostic aphasia examination - Chinese version (BDAE-C) after intervention and follow-up. The Modified Barthel Index (MBI), 36-Item Short Form Health Survey (SF-36), and results of blood oxygen level dependent-functional magnetic resonance imaging (BOLD-fMRI) examination are considered as the secondary outcome measures. Other outcomes will include rate of adverse events and economic effects.

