A limitation of this study is that this protocol is not double-blind and has no placebo control. However, the intervention group will be blinded to the evidence-based medicine center to decrease possible bias. The study also cannot eliminate the confounding effects from the spontaneous recovery in the early stage of stroke.

If successful, this project will offer a low-cost appropriate technology for the CHCs and could be implemented on a large scale, both in China and worldwide. Scalp acupuncture therapy, which can be performed in a CHC instead of in a high-grade hospital, will relieve the stress of hospitalization and reduce the financial burden for the patient and healthcare system.

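### The only stated summary for a proportion is its standard error, which fails for rare adverse events: with 0 events in about 145 patients it is 0, while the exact 95% interval reaches 2.5%.

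*Protocol article*

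**What the plan says.** The Statistical methods section of the protocol article sets a general descriptive rule: "Descriptive statistics will be expressed in different forms according to the types of the data in each group". For categorical data it specifies that "categorical variables will use proportions with their standard error". No confidence interval is named for any proportion.

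Adverse events appear in three other places. The abstract states: "Other outcomes will include rate of adverse events and economic effects". Safety assessments adds: "Any adverse event will be analyzed regardless of the causality related to intervention". Statistical methods fixes the analysis set: "The safety set (SS) will be used to assess adverse events". The sentence on between-group tests, which begins "Comparison of baseline characteristics, the primary or secondary outcomes between groups will use the", does not mention adverse events.

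Proportion with standard error is therefore the only stated summary that reaches an adverse-event rate.

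**The concern.** Whether a patient had a given adverse event is a categorical variable, so the general rule applies to it unless something else is said. The usual standard error of a proportion is estimated from the observed proportion itself. It collapses to zero when no event is seen and misleads when there are only one or two. For uncommon harms, these are the counts on which a statement about tolerability would rest.

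This matters because the Discussion says the combined treatment will be examined "from the view of safety and efficacy", and that, if successful, it "could be implemented on a large scale, both in China and worldwide". A table line showing 0% with a standard error of 0 would give readers of such a recommendation no indication of the risk that the trial could not exclude.

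**Working it through.** **Inputs**
- Total sample 290, with a 10% dropout allowance (Sample size).
- Only the experimental group is needled (Study design). With equal arms this is 290 / 2 = 145 patients. Equality is an assumption, because whole community health centres (CHCs) are allocated.
- Cluster size m = 16 and intra-CHC correlation ρ = 0.030 (Sample size).
- Rates of 64.71% and 85%, α = 0.05, power 90% (Sample size), two-sided (Statistical methods).

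**The plan's own figure**

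The stated formula without clustering gives (1.960 + 1.282)² × (0.6471 × 0.3529 + 0.85 × 0.15) / 0.2029² = 90.83. The design effect is 1 + 15 × 0.03 = 1.45, and 90.83 × 1.45 = 131.70. This gives 132 per group, as stated. Then 264 × 1.1 = 290.4, which agrees with 290. Dividing instead, 264 / 0.9 = 293.3; the difference is immaterial here.

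**No events in 145**
- Standard error: √(0 × 1 / 145) = 0.
- Exact two-sided 95% upper limit: 1 − 0.025^(1/145) = 2.51%.
- If only 132 patients are in the set: 1 − 0.025^(1/132) = 2.76%.

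**One to three events in 145**

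The simple interval is p ± 1.96 × √(p(1 − p)/145). The exact interval is Clopper-Pearson.

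| Events | Proportion | Standard error | Simple 95% interval | Exact 95% interval |
|---|---|---|---|---|
| 1 | 0.69% | 0.69% | −0.66% to 2.04% | 0.02% to 3.78% |
| 2 | 1.38% | 0.97% | −0.52% to 3.28% | 0.17% to 4.89% |
| 3 | 2.07% | 1.18% | −0.25% to 4.39% | 0.43% to 5.93% |

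In each row the simple interval starts below zero and its upper end is too low. At one event, the upper end is 2.04% where the exact limit is 3.78%.

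**How easily zero can arise**

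The chance of no event among 145 independent patients is (1 − risk)^145. It is 0.48 at a true risk of 0.5%, 0.23 at 1% and 0.05 at 2%.

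**Clustering, as an illustration only**

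If the design effect of 1.45 also held for adverse events, the effective number would be 145 / 1.45 = 100. The upper limit for zero events would be 1 − 0.025^(1/100) = 3.62%.

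**The case against.** The strongest reply is that the quoted rule is generic. It does not name adverse events, and the sentence that does name them fixes only the analysis set. Interval methods for safety tables are commonly left to a full protocol or analysis plan, neither of which is shown, and nothing in the article forbids an exact interval. It stands that applying the rule to adverse events is an inference from its general wording. The reply does not remove the point, because the article does state a summary for proportions, exempts nothing from it, and that summary suits rare events badly.

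Several further objections stand and limit the point:
- The documents give no expected adverse-event rate, so a count of zero to two for any event type is an assumption. All events are analysed whatever their cause, over 4 weeks of treatment and 12 of follow-up in stroke patients. The overall proportion with any event may well not be rare, and there a standard error works adequately.
- A reader might infer that an empty table would be taken as proof of safety. No section says so and there is no safety decision rule. The Discussion sentence on safety and efficacy goes on to a cost-effectiveness comparison, and the remark on wide use is conditional on success. A reader given the count 0 of 145 could also derive the upper limit.
- The intra-CHC correlation was given for the effective rate, not for harms. With no events it cannot be estimated from the trial. The 3.6% limit is therefore not a figure of the plan.

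**Conclusion.** The point holds as a minor one about reporting. The only stated summary for a proportion covers adverse-event rates by its general wording and is uninformative when an event type is rare or absent. With 0 of about 145 it shows an error of 0, where the data remain compatible with a risk of up to 2.5%. With 1 of 145 it implies an interval of −0.7% to 2.0%, against an exact 0.02% to 3.8%.

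These sizes assume equal arms, patients treated as independent, and a very low count for the event type in question. The document does not support the stronger reading that it prescribes a standard error for adverse events by name, or that it would declare the treatment safe on an empty table. The sample size and the analysis of the primary outcomes are unaffected.

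**What to change.** In Statistical methods, add one sentence: adverse events will be reported per arm on the safety set as the number of patients with an event, the proportion and an exact (Clopper-Pearson) 95% confidence interval, in place of the standard error. Any safety conclusion should state the upper limit, so that readers see which risk has and has not been excluded.

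An allowance for clustering by CHC can be given as a sensitivity figure, with the assumed design effect stated. It should not be a mandatory adjustment, since no correlation for adverse events is available.

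The cost is one sentence and trivial computation, with no new data. The downside is a slightly less favourable safety statement.

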## Methods/Design

### Study design

The current study uses a multicentre, cluster randomized, parallel-controlled superiority design with blinded assessment (a flow diagram of the study design is presented in Figure 
1). The course of this trial will comprise a 4-week intervention and a 12-week follow-up period. The control group will receive SLT and initial therapies, while, the experimental group will receive additional scalp acupuncture. There is a total of five time points, including baseline, 2 weeks after treatment, 4 weeks after treatment, 6 weeks after follow-up, and 12 weeks after follow-up. Fujian University of Traditional Chinese Medicine (FJTCM), as an undertaker of this project, is responsible for completing the training of the rehabilitation therapists in a unified standard way before the study, and supervising their operations regularly during the study at all clinical sites. The Center of Evidence-based Medicine in FJTCM, which plays a role in randomization and will be blinded to the intervention, is an independent department employed to monitor and analyze data. The present project, funded by the State Administration of Traditional Chinese Medicine, has received approval from the local ethics committees of every center (Fujian: 2013KY-006-01, approval received in July 2013; Henan: 2014HL010, approval received in March 2014; Shandong: 2013KY-006-01, approval received in March 2014) participated in the study. Written informed consent is required prior to participation from each participant or their guardian, and they will be informed of the nature of this trial including its purpose, procedures involved, expected duration, potential risks and discomfort, as well as the possible benefits they will receive from it. There is no time limit for them to ask related questions and respond to the invitation to participate. Participants will be also informed that they are free to withdraw from the study at any stage for any reason and their personal information will be undisclosed and kept securely at FJTCM.

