### Sample size

Referring to a trial
[23] with the same protocol as the present study, the effective rate of Broca’s aphasia after stroke was 64.71% in the control group (π_1_) and 85% in the experimental group (π_2_). Preliminary epidemiological findings show that there will not be less than 16 qualified participants recruited from each CHC. Prior data indicates that the intra-CHC correlation coefficient (ρ) is likely to be 0.030. Each group will consist of 132 individuals according to the formula:

(1)$$n=\frac{{\left(\mu_{\alpha }+\mu_{\beta }\right)}^{2}\;\left[\pi_{1}\;\left(1-\pi_{1}\right)+\pi_{2}\;\left(1-\pi_{2}\right)\right]\left[1+\left(m-1\right)\;\rho \right]}{{\left(\pi_{1}-\pi_{2}\right)}^{2}}$$

with a type I error of 5% (α = 0.05) and 90% power (β = 0.10). There will be 290 subjects included in total, allowing for a dropout rate of 10%.

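### Community health centers are randomised as clusters, but the outcomes are compared with patient-level tests that ignore clustering; at the plan's own inputs a nominal 5% test has about 10% type I error

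*Protocol article*

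**What the plan says.** The Study design section calls the trial a "multicentre, cluster randomized, parallel-controlled superiority design with blinded assessment". The Randomization and blinding section fixes the unit: "Each participating CHC will be assigned to either experimental group or control group by restricted randomization". The Sample size section follows suit. It states "Prior data indicates that the intra-CHC correlation coefficient" is likely to be 0.030, takes at least 16 participants per CHC, and multiplies the two-proportion formula by 1+(m−1)ρ to reach 132 per group, "with a type I error of 5% (α = 0.05) and 90% power (β = 0.10").

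The Statistical methods section departs from this. It applies one set of simple two-group tests to baseline, primary and secondary variables alike. The list begins with the t-test, goes on "or Mann-Whitney test for continuous variables and Pearson chi-squared or", and ends with the exact test of Fisher. The threshold is "two-sided *P* < 0.05 was considered statistically significant". The article mentions no random CHC effect, generalised estimating equations, CHC-level summary or cluster-robust variance.

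The Methods/Design paragraph of the abstract describes a different unit: "290 eligible patients with aphasia due to stroke will be randomly allocated into a control group or an experimental group".

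**The concern.** When CHCs are randomised, patients in the same CHC share therapists, assessors and catchment as well as treatment arm. Their outcomes are correlated, and the between-group difference varies more than it would with independent patients. The named tests estimate its variance as if there were no such correlation. Their P values are then too small, and the error runs in one direction: towards declaring superiority when there is none.

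This affects every between-group efficacy comparison, including both primary scales. The article says that a positive result would support large-scale use in China and elsewhere. The sponsor also recruits about 45% more patients to allow for the correlation and then leaves it out of the analysis.

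This is not a detail left to a separate analysis plan. The article names the tests for the primary outcomes, and they conflict with its own design and sample size sections.

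**Working it through.** **Inputs from the Sample size section.** π₁ = 0.6471, π₂ = 0.85, m = 16 (stated as a minimum), ρ = 0.030, α = 0.05, power 90%, dropout 10%. Two-sided testing comes from Statistical methods.

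**Step 1: reproduce the plan's sample size.**
- Variance term: 0.6471 × 0.3529 + 0.85 × 0.15 = 0.3559.
- Squared difference: (0.85 − 0.6471)² = 0.04117.
- (1.960 + 1.282)² = 10.507.
- Without clustering: 10.507 × 0.3559 / 0.04117 = 90.8 per group.
- Design effect: 1 + (16 − 1) × 0.03 = 1.45.
- With clustering: 90.83 × 1.45 = 131.7, which rounds up to the stated 132.
- Total: 264 × 1.1 = 290.4, the stated 290.

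The figure reproduces with two-sided α. A one-sided α would give 107.3. The plan therefore does rely on a design effect of 1.45.

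**Step 2: true size of the unadjusted test.** The true variance of the difference is 1.45 times what the test assumes, so the standard error is understated by √1.45 = 1.204. An interval built on it would be 1 − 1/1.204 = 17% too narrow. The nominal cut-off of 1.96 behaves like 1.96 / 1.204 = 1.628 true standard errors:

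2 × [1 − Φ(1.628)] = 0.104, or 10.4%.

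**Step 3: sensitivity to ρ and cluster size.** Same formula:

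| Patients per CHC | ρ | Design effect | Type I error |
|---|---|---|---|
| 16 | 0.01 | 1.15 | 6.8% |
| 16 | 0.02 | 1.30 | 8.6% |
| 16 | 0.03 | 1.45 | 10.4% |
| 16 | 0.05 | 1.75 | 13.8% |
| 14.4 (after 10% dropout) | 0.03 | 1.40 | 9.8% |
| 20 | 0.03 | 1.57 | 11.8% |
| 30 | 0.03 | 1.87 | 15.2% |

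**Step 4: simulation under no treatment effect.** The article does not give the number of CHCs. Dividing 132 to 145 patients per arm by 16 suggests 8 or 9. With 9 CHCs of 16 per arm and ρ = 0.03, the rejection rates at nominal 5% were:
- t-test on patients: 10.5%
- chi-squared: 10.6% to 10.7%
- Mann-Whitney: 10.8%
- t-test on CHC means, same data as the patient t-test: 5.2%, which is 5% within simulation error

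**Step 5: power of a correct test.** Take the plan's effect, a design effect of 1.45, and 18 − 2 = 16 degrees of freedom (critical value 2.12).
- 132 per arm: standard error √(0.3559 × 1.45 / 132) = 0.0625, standardised difference 0.2029 / 0.0625 = 3.25, power 86%.
- 144 per arm (9 × 16): standard error 0.0599, standardised difference 3.39, power 89%.

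**The case against.** The core is hard to dispute, but the size can be questioned.

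- **ρ is carried across outcomes.** The 0.030 is given beside an effective rate, while the primary outcomes are the CRRCAE score and the BDAE-C grade, for which no ICC is stated. This stands, and it is why the range in Step 3 belongs with the headline figure. The chi-squared result likewise applies to a binary outcome, and none is listed as primary or secondary.
- **CHC number and size are not fixed.** The count is inferred and 16 is a minimum. The 10.4% does not depend on the count. Larger clusters raise the error, and 10% dropout lowers it only to 9.8%.
- **The randomisation is restricted, in a way not described.** If CHCs were balanced within the three provinces (an assumption), variation between provinces would cancel. In simulation with 9 CHCs of 16 per arm and total ρ = 0.03, the t-test error was about 8.5% if one third of the between-CHC variance lay between provinces, and about 7.5% if half did. This stands as a reason not to treat 10% as exact, but the inflation remains.
- **The figure is per test.** There are two primary scales at several time points and no stated decision rule, so the error of the overall conclusion could be higher or lower.
- **The abstract is a condensed text.** The body consistently describes CHC randomisation, so the abstract is a minor wording error beside the choice of tests.

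The tests could in principle be meant for CHC-level summaries. Nothing in Statistical methods says so, and the section speaks of patient data and patient analysis sets throughout.

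**Conclusion.** The concern holds and must be fixed. The stated between-group tests contradict the article's own design and sample size. At its own m = 16 and ρ = 0.030, a nominal 5% test has a true type I error of about 10.4%. This assumes that the same ρ applies to the score outcomes, that clusters are of equal size, and that the restriction on randomisation removes no between-CHC variance. Varying ρ from 0.01 to 0.05 gives 6.8% to 13.8%; no value of ρ or cluster size examined, nor the province-balanced allocation, brings the error back to 5%.

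**What to change.** Replace the between-group tests in Statistical methods with methods that respect the CHC as the unit of randomisation:
- **Scores (CRRCAE, MBI, SF-36):** a linear mixed model with a random CHC effect and small-sample degrees of freedom, about the number of CHCs minus 2. A t-test on CHC means is a simple alternative. The two agree exactly only when clusters are equal in size, so the mixed model is preferable if sizes vary.
- **BDAE-C grade (0 to 5) and any binary outcome:** an ordinal or logistic model with a random CHC effect, or generalised estimating equations with a small-sample correction.
- **Proportions:** report cluster-robust standard errors.
- **Restriction factors:** state what the randomisation was restricted on, and include those factors in the model.
- **Abstract:** say that CHCs, not patients, are randomised.

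The cost is analysis wording and one corrected sentence. Each patient's CHC is already known, so no new data are needed. The sample size already carries the design effect, but with about 18 CHCs the small-sample degrees of freedom bring power to roughly 86% to 89% instead of 90%, and the plan should say so. The change should be made before the unblinded analysis.
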